### Control treatment – treatment as usual

The control treatment consists of receiving the treatment that would have been available without participation in the trial, i.e. treatment as usual. The patient's case manager will carry out the control treatment. In essence, treatment as usual for cannabis abuse is part of the existing, manualized psychosocial and/or pharmaceutical treatment for psychotic illness; however, no explicit manual exists on ways in which cannabis abuse should be approached. Treatment as usual is thus not expected to be uniform. In particular, frequency of contacts may vary between case managers, and this will be registered and analyzed. However, the heterogeneous nature of the control treatment accurately reflects the current situation in Denmark, and we therefore consider this to be the appropriate treatment for analytical control.

Treatment as usual is carried out in one of three established facilities; the OPUS teams for early detection and treatment of young people with psychosis [35], the community mental health centers (CMHC) [36], and the assertive community treatment (ACT) teams [37]. The effect of treatment as usual on cannabis abuse in Denmark is unknown, but a randomized trial comparing OPUS treatment with other treatment (primarily CMHC) investigated prevalence of any comorbid diagnosis of harm or dependence syndrome at baseline and at one and two years follow-up. At baseline, 27% in both treatment arms had such a comorbidity, which decreased to 16 – 17% for OPUS patients and 21 – 22% for other patients [38].

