### Sample size and power calculation

A 2008 Cochrane review of psychosocial interventions for people with both severe mental illness and substance misuse [28] identified five papers with results from studies using a combination of motivational interviewing and cognitive behavioral therapy.[22,64-67] However, only one of these contains information about reduction of days with cannabis abuse, but presents only the median, not the mean, and the range, not the standard deviation.[22] However, 6 months after start of treatment, this particular paper reported that those receiving integrated care had, as median, 20.62 percent of days abstinent from all substances, compared to 1.10 in the routine care group, i.e. a difference of 19.5. Extrapolating this to our study, with a TLFB-period of 30 days, corresponds to 5.85 days. Truncating this to a more conservative 5 days, and assuming a standard deviation also of 5 days, it becomes possible to calculate sample size for an independent samples t-test; with an α-level of 0.05 and a power of 0.90, the required number of patients in each intervention can be calculated to be 22. Due to attrition, more patients will be required. Results from the OPUS trial, which may be comparable to our study in terms of participant profiles, showed that high attrition may be expected among substance-using people with schizophrenia [38]. We obtained data about one-year dropout from the OPUS trial among people with substance misuse, and found that among those receiving the control treatment, the dropout-rate was 37%. Generalizing this to our study, regardless of intervention allocation, at least 35 patients will be required in each of the two intervention groups. However, we aim to include between 60 and 70 patients in each group, as this would enable us to stratify the analyses. With 60 or 70 patients, it should also be possible to measure even smaller differences in secondary outcomes.

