### Statistics

The main null-hypothesis to be tested is that there is no difference between the two treatment arms with regard to decrease in cannabis use. All randomized patients will be analyzed, including those who stop receiving treatment, according to the intent-to-treat principle [68]. Continuous outcome measures, including the primary outcome of reduction of days with cannabis abuse, will be analyzed using multivariate analysis of variance (ANOVA) mixed models with repeated measurements. This will include interaction analyses of time and type of treatment, in order to evaluate the effect over time. Binary outcome measures will be analyzed using multivariate logistic regression models. The subgroup of patients who complete the entire experimental treatment will be compared with all those randomized into the trial in order to determine risk factors for attrition. Sensitivity analyses will be carried out to evaluate the effect of treatment in patients that are inaccessible for follow-up. This will be conducted by multiple imputation methodology both using last observation carried forward, and assuming an increase in cannabis use among those lost to follow-up.

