## Discussion

The centralized randomization procedure offers strengths to the CapOpus trial by reducing the risk of selection and allocation bias [71,72]. The outcome assessments are blinded with the intent of being unbiased [71,72]. The planned intense follow up of patients coupled with intention-to-treat analyses should guard against attrition bias [71,72]. Also, the broad array of outcome estimates allows us to measure effects of treatment in many areas of life.

Apart from gathering evidence about best practice in treatment of cannabis abuse among young people with psychosis, the study will allow us to validate the TLFB measurement tool for cannabis against blood samples, something that to our knowledge has not been done previously.

Hopefully, the CapOpus intervention will carry positive effects. If this is so, this could substantially improve treatment of these patients. On the other hand negative consequences cannot be ruled out. The extra interventions in the experimental arm may potentially cause more patients to drop out from usual treatment. Should this occur, the addiction consultants in CapOpus will actively support the patients in resuming contact with the case managers.

Our trial may have several limitations. First, it is a rather small trial aiming at demonstrating a substantial intervention effect. In a sense, our trial may be viewed as a pilot for potentially larger trials at a later stage. Second, the large number of outcomes makes interpretation of significant findings difficult. Accordingly, our interpretation of significant findings at or close to the conventional level of p = 0.05 will be conservative. One further limitation of the trial is that there may be a crossover relating to the patients' case-managers. Due to the randomization procedure, the same case manager may have patients in both the experimental intervention and the control treatment arms. This spawns the risk that elements from the experimental intervention are incorporated into the treatment of patients in the control arm, potentially leading towards type II errors. It will be attempted to bypass this limitation by investigating outcome differences between control-group patients whose case managers also have patients in the CapOpus experimental intervention arm, and those whose case managers do not.

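### The missing-data sensitivity analysis names last observation carried forward as multiple imputation, and sets the treatment effect in patients with baseline data only to zero

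*Protocol article*

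**What the plan says.** The Statistics section gives the primary outcome a repeated-measures analysis: continuous outcomes "will be analyzed using multivariate analysis of variance (ANOVA) mixed models with repeated measurements", with a time-by-treatment interaction. The population is intention-to-treat: "All randomized patients will be analyzed, including those who stop receiving treatment, according to the intent-to-treat principle".

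For missing follow-up it then adds: "Sensitivity analyses will be carried out to evaluate the effect of treatment in patients that are inaccessible for follow-up". The method is fixed in the next sentence: "conducted by multiple imputation methodology both using last observation carried forward, and assuming an increase in cannabis use among those lost to follow-up". There are thus two scenarios, both called multiple imputation.

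Under Assessments, TLFB days are collected at baseline, 6 months and 10 months only. Under Sample size and power calculation, the authors take one-year dropout among substance-misusing patients of the OPUS trial, where they "found that among those receiving the control treatment, the dropout-rate was 37" per cent, and apply that rate to both arms. The Discussion states: "The planned intense follow up of patients coupled with intention-to-treat analyses should guard against attrition bias".

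**The concern.** Multiple imputation draws several plausible values for each missing outcome and adds the variance between the completed data sets to the variance within them. LOCF gives the same value every time. The between-imputation variance is zero and Rubin's rules have nothing to combine. A reader of the results would be told that the uncertainty from missing data had been carried through when it had not.

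The scenario also cannot do the job set for it. With two follow-up visits, a patient lost before 6 months has only the baseline value to carry forward. Change is then exactly zero in either arm, and the treatment effect in these patients is zero by construction, whatever the truth. If more than a third of patients are lost, this weighs heavily on the estimate, and the claim to guard against attrition bias is left without a sound test from this scenario.

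**Working it through.** **Inputs from the protocol** (Sample size and power calculation): difference 5 days, SD 5 days, α 0.05 (sidedness not stated; two-sided reproduces the figure), power 0.90, loss d = 0.37 in both arms, target 60 to 70 per arm.

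**Assumptions not in the protocol:** SD 5 applies to change; changes are normal; loss is at random; those lost have only a baseline value.

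**1. The plan's own figures.** n = 2 × (1.960 + 1.282)² × 5²/5² = 21.0, rounded up to 22 per arm (the t-test solution is 22.02). Allowing for loss, 22/(1 − 0.37) = 34.9, so 35. Both stated figures reproduce. The protocol gives no figure for the missing-data analysis itself.

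**2. Estimate under LOCF.** If the mean change in an arm is μ, LOCF has expectation (1 − d)μ. With equal loss the difference becomes (1 − d) × 5:
- 37% lost: 0.63 × 5 = 3.15 days
- 20% lost: 0.80 × 5 = 4.0 days
- 10% lost: 0.90 × 5 = 4.5 days

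**3. Standard error with a true 5-day effect and 37% lost.** The per-patient variance under LOCF is (1 − d)σ² + d(1 − d)μ². The observed-case SE is √[2σ²/(n(1 − d))].
- *No improvement in control, n = 60 per arm.* Variances: 15.75 + 0.2331 × 25 = 21.58, and 15.75. LOCF SE = √(37.33/60) = 0.79. Observed cases: √(50/37.8) = 1.15. Simulated proper multiple imputation (20 imputations, Rubin's rules): estimate 5.0 days, SE 1.18, with between-imputation variance about 37% of the total. The LOCF SE is 0.67 times the multiple-imputation SE, one third smaller. In simulation the LOCF interval covers the true 5 days about 35% of the time.
- *Common 5-day improvement, n = 65 per arm.* Mean changes are 10 and 5. Variances: 15.75 + 0.2331 × 100 = 39.06, and 21.58. LOCF SE = √(60.64/65) = 0.966. Observed cases: √(50/40.95) = 1.105. The ratio is 0.87, so LOCF is about 13% smaller. Had nobody been lost, the SE would be √(50/65) = 0.88, so here LOCF is not narrower than complete data.

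**4. No true effect, equal loss.** The expected difference is zero. Simulated type I error is about 5%.

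**5. No true effect, unequal loss.** The spurious difference is m × (difference in loss), where m is the improvement common to both arms. Take 20% lost in the experimental arm and 37% in control (the 20% is an assumption), SD 5, 65 per arm:
- m = 5 days (assumption): 5 × 0.17 = 0.85 days; simulated rejection about 18% at nominal 5% (11% at SD 8, 9% at SD 10).
- m = 0.33 days: 0.33 × 0.17 = 0.06 days; simulated rejection 5.1%. The 0.33 is 1.10% of 30 days, from the routine-care median that the protocol cites. That figure is a level of abstinence from all substances, not a change in cannabis days, so it serves only as a low illustration.

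The sign follows the arm that loses more. With 27% vs 47% loss, m = 5 and 60 per arm, the spurious difference is about 1 day in either direction, with rejection of 21–22%.

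**6. If lost patients really stay at their last value.** Across the simulated scenarios the LOCF SE agrees with the sampling SD of its own estimate (0.787 vs 0.785 at n = 60, true effect 5 days). Under that assumption the interval is valid.

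**The case against.** The strongest reply is that this is one of two sensitivity scenarios. The primary mixed model uses all randomized patients and no carried-forward values, so the trial's main estimate is untouched. That stands. It also stands that LOCF, declared as a no-change scenario, is coherent, and that its interval is valid if the assumption is true.

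A reader might infer that the plan biases the trial result, produces falsely narrow intervals as a matter of course, or creates an effect where there is none. The documents do not support this. Attenuation and understated uncertainty depend on why patients are lost. The protocol applies the same loss to both arms, and then the bias is toward no effect. A spurious effect needs both unequal loss and a common improvement, and the protocol fixes neither. The earlier trial is only indirect support for a common improvement: "At baseline, 27% in both treatment arms had such a comorbidity", falling to 16–17% and 21–22%, but that is prevalence of a comorbid diagnosis at one and two years, not cannabis days at 6 months.

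The 37% is also a one-year rate from another trial's control arm. This trial assesses at 6 and 10 months and plans intense follow-up. A patient seen at 6 months would carry that value, not baseline, to 10 months. Step 2 may therefore overstate the loss of effect.

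Finally, the size of the assumed increase, and whether it differs by arm, are details that a condensed article may leave to a fuller document. No fault is claimed there. None of this removes the contradiction in the stated method, which the article itself fixes.

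**Conclusion.** The point holds as a moderate one. The protocol names a deterministic single imputation as multiple imputation, and the resulting scenario cannot evaluate the treatment effect in patients with baseline data only, because it sets that effect to zero.

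At 37% loss at random in both arms, with baseline values only for those lost, a true 5-day effect would be reported as about 3.15 days. The SE at SD 5 would be roughly 13% smaller (5-day common improvement, against observed cases) to one third smaller (no common improvement, against proper multiple imputation). These sizes rest on the assumptions listed in the working and shrink with less loss or with 6-month values available. There is no inflation of type I error under equal loss, and no effect on the primary analysis.

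**What to change.** Replace the sentence on method so that it says, in substance:
- Missing 6- and 10-month TLFB days are imputed by proper multiple imputation within arm, from baseline days, severity stratum, referrer and any observed follow-up, and combined by Rubin's rules.
- The increased-use scenario is a delta-adjusted version of that imputation. A stated range of extra days of use is added to the imputed values, bounded at 30 days and allowed to differ by arm, and the tipping point is reported.
- LOCF is dropped, or kept only as a labelled single-imputation, no-change scenario.

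The cost is rewording and some programming, with no new data. Intervals will be wider than LOCF would have shown.

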### Ethical considerations

The regional ethics committee for the greater Copenhagen area has approved the protocol under the file number H-D-2007-0028, as has The Danish Data Protection Agency under the file number 2007-41-0616. The trial is registered at ClinicalTrials.gov as NCT00484302. Both positive and negative findings from the trial will be published, in accordance with the CONSORT guidelines [69,70].

Information about the trial is presented to potential participants both verbally and in written form. It is stressed that participation is voluntary, without expected negative side effects, and that the patient can withdraw his or her consent at any time without consequence for treatment possibilities. Patients will receive a copy of their rights.

## Discussion

The centralized randomization procedure offers strengths to the CapOpus trial by reducing the risk of selection and allocation bias [71,72]. The outcome assessments are blinded with the intent of being unbiased [71,72]. The planned intense follow up of patients coupled with intention-to-treat analyses should guard against attrition bias [71,72]. Also, the broad array of outcome estimates allows us to measure effects of treatment in many areas of life.

Apart from gathering evidence about best practice in treatment of cannabis abuse among young people with psychosis, the study will allow us to validate the TLFB measurement tool for cannabis against blood samples, something that to our knowledge has not been done previously.

Hopefully, the CapOpus intervention will carry positive effects. If this is so, this could substantially improve treatment of these patients. On the other hand negative consequences cannot be ruled out. The extra interventions in the experimental arm may potentially cause more patients to drop out from usual treatment. Should this occur, the addiction consultants in CapOpus will actively support the patients in resuming contact with the case managers.

Our trial may have several limitations. First, it is a rather small trial aiming at demonstrating a substantial intervention effect. In a sense, our trial may be viewed as a pilot for potentially larger trials at a later stage. Second, the large number of outcomes makes interpretation of significant findings difficult. Accordingly, our interpretation of significant findings at or close to the conventional level of p = 0.05 will be conservative. One further limitation of the trial is that there may be a crossover relating to the patients' case-managers. Due to the randomization procedure, the same case manager may have patients in both the experimental intervention and the control treatment arms. This spawns the risk that elements from the experimental intervention are incorporated into the treatment of patients in the control arm, potentially leading towards type II errors. It will be attempted to bypass this limitation by investigating outcome differences between control-group patients whose case managers also have patients in the CapOpus experimental intervention arm, and those whose case managers do not.

The fact that the current treatment in Denmark is not uniform is reflected in the control treatment, as no attempts will be made to artificially introduce a level of homogeneity in this intervention arm. This may, however, lead to a degree of selection bias if only a small proportion of eligible case managers actually refer patients to the trial. Results will be interpreted accordingly.

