## Background

A recent meta-analysis of eleven longitudinal studies concluded that cannabis use is associated with increased risk of lasting psychotic conditions later in life [1]. Assuming causality, as much as 800 annual cases of schizophrenia are preventable in the UK if exposure to cannabis was eliminated [2]. Several studies have shown that use of cannabis increases the risk of developing schizophrenia-like symptoms, especially in young men disposed to developing psychosis [3-10]. Furthermore, use of cannabis among patients with psychosis can maintain and worsen the psychotic symptoms [11-15], and comorbid schizophrenia and substance abuse is associated with lack of compliance to treatment and with more rehospitalizations [15-20]. This indicates both that effective interventions to limit cannabis use in persons with psychosis are needed, and that getting patients to follow such interventions may be difficult.

A randomized trial showed that the combination of cognitive behavioral therapy, motivational interviewing [see [21]], and family involvement had a significant positive effect on level of functioning, psychotic symptoms, and duration of periods of cannabis-abstinence, compared with regular treatment [22]. This finding has been supported by two reviews, concluding that positive evidence exists for integrated treatment with motivational interviews, cognitive behavioral therapy (individual or group-based), and a harm-reduction approach [23,24]. Group-based treatments are arguably less expensive, and in a literature review, Weiss et al. concluded that specialized group therapy could reinforce the effect of an existing treatment [25]. However, there is currently insufficient evidence to show that group-based interventions for cannabis use are superior to individual treatment [26,27]. Similarly, authors of a recent Cochrane review concluded that insufficient evidence exists to show that any psychosocial treatment method for comorbid schizophrenia and substance abuse is superior to others [28].

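### Intention-to-treat does not by itself guard against attrition bias: for patients never assessed the result rests on a missing-data assumption, and the planned carried-forward analysis tests it poorly

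*Protocol article*

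**What the plan says.** The Discussion of the protocol article lists this among the trial's strengths: "The planned intense follow up of patients coupled with intention-to-treat analyses should guard against attrition bias".

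The Statistics section sets the analysis rule: "All randomized patients will be analyzed, including those who stop receiving treatment, according to the intent-to-treat principle". The primary outcome, cannabis days in a 30-day window on the Time-Line Follow Back (TLFB), goes into a repeated-measures mixed model with a time-by-treatment interaction. No covariates are listed. For patients who cannot be followed up, the same section plans sensitivity analyses under the name of multiple imputation. One carries the last observation forward and the other assumes that cannabis use rose. Risk factors for attrition are also to be examined.

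The Sample size section takes its dropout figure from substance-misusing patients in an earlier trial over one year: "among those receiving the control treatment, the dropout-rate was 37"%. It applies this to both arms and concludes that "at least 35 patients will be required in each of the two intervention groups", with 60 to 70 per arm as the recruitment aim.

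Other sections describe data that do not need the patient at a study visit. Outpatient treatments and bed days come from national registers in both arms (Other assessment tools). For usual care, "frequency of contacts may vary between case managers, and this will be registered and analyzed". Contacts with the trial's consultants are counted in the CapOpus arm only. The stated uses are cost, description of usual care, and adherence. The text gives none of them a role in handling missing cannabis data.

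**The concern.** The Discussion credits the analysis with a property that it does not have. Keeping every randomised patient in the assigned arm prevents bias from excluding people who stop treatment. It says nothing about what the cannabis count would have been in someone who was not assessed. A patient lost before month 6 and not seen at month 10 has one TLFB value, at baseline. The model in effect assigns that patient the expected course of similar patients in the same arm who were seen. That is right only if loss is unrelated to later cannabis use, given what the model contains.

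The article gives reasons for doubt. Its Background notes that "comorbid schizophrenia and substance abuse is associated with lack of compliance to treatment and with more rehospitalizations". Only the CapOpus arm has consultant contact and reinforcement for attendance, and the Discussion itself fears that the extra interventions may drive some patients out of usual treatment. Loss could therefore differ between arms in amount or in kind, which is what biases a treatment contrast.

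The carried-forward check does not probe this. For a patient lost before month 6 it enters a change of exactly zero and treats that value as known. It is a single imputation, so it carries none of the uncertainty that multiple imputation is meant to carry.

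**Working it through.** **1. The plan's own figures.** Inputs from the Sample size section: "Truncating this to a more conservative 5 days, and assuming a standard deviation also of 5 days", and "with an α-level of 0.05 and a power of 0.90, the required number of patients in each intervention can be calculated to be 22". The normal formula gives n = 2 × (1.960 + 1.282)² × 5² / 5² = 21.01, rounded up to 22 per arm. The exact two-sided t-test needs 22.02, and its power at 22 is 0.900. Dropout: 22 / (1 − 0.37) = 34.9, so 35. Both figures reproduce. The inflation treats dropouts as contributing no outcome, so the plan itself reckons with missing cannabis counts at this rate.

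**2. How many patients this concerns.** At 37%: 0.37 × 60 = 22.2 and 0.37 × 70 = 25.9, so about 22 to 26 lost and 38 to 44 observed per arm. Power for 5 days with SD 5 is then still 0.99 or more. The threat is bias, not power.

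**3. Size of the bias.** Each arm's estimated mean is 0.63 × (mean of the observed) + 0.37 × (model's prediction for the lost). Its error is 0.37 × (prediction − truth among the lost). With 37% lost in both arms, bias in the contrast = 0.37 × D, where D is the between-arm difference in that departure.

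| D (days) | Bias (days) | Share of the 5-day target |
|---|---|---|
| 0 | 0 | 0% |
| 1 | 0.37 | 7% |
| 2.5 | 0.93 | 19% |
| 5 | 1.85 | 37% |

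The documents give no value for D.

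**4. What carrying forward does.** Suppose all 37% are lost before month 6 and would have had the same 5-day difference as everyone else. Carrying baseline forward sets their difference to 0, so the estimate becomes 0.63 × 5 = 3.15 days. The method creates a 1.85-day error even though loss was harmless.

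**5. What auxiliary variables could gain.** All of this is illustration under assumed values: true effect 5 days, SD 5, loss driven by engagement after randomisation.

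- Large sample, 37% loss in both arms, engagement–outcome correlation 0.7 in CapOpus and 0.3 in control: bias about +0.8 days. An auxiliary variable correlated 0.5, 0.7 or 0.85 with engagement reduces it to about 0.65, 0.46 or 0.27.
- Large sample, 47% loss in control and 27% in CapOpus, correlation 0.5 in both: bias about −0.5. The same auxiliaries shrink it to about −0.4, −0.3 or −0.2. Swapping the arms reverses the sign.
- Same mechanism in both arms: bias about 0 with or without auxiliaries.

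**6. Price in precision at 65 per arm.** In a separate simulation the auxiliary drives loss, in the same way in both arms, but is unrelated to the outcome. Using it raises the standard error from 0.97 to 1.09. The length of the list matters too. With one informative auxiliary and six uninformative ones, root mean square error goes from 1.33 to 1.30 (correlation 0.5) or 1.31 to 1.18 (0.85) in the first scenario of step 5. In the unequal-loss scenario it goes from 1.24 to 1.26 or 1.20 to 1.24. A long list largely cancels the gain; a short one does not.

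**The case against.** The strongest reply is that the sentence names two things, and intense follow-up comes first. Less loss is the most direct protection there is, and the wording is hedged. That stands, and the sentence should keep that half. It does not rescue the other half, because the plan still allows for 37%.

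A reader might go further and infer that the intention-to-treat rule keeps only patients who stop treatment. It does not say that. It covers all randomised patients and names treatment stoppers as an included case.

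A reader might also infer that lost patients are modelled from earlier TLFB values alone, while data known to predict their cannabis use lie unused. The documents do not support this. Covariates and imputation variables are not listed and may be in an analysis plan that is not shown. A patient missed at month 6 but seen at month 10 contributes a later value. The assumed-increase scenario is a genuine missing-not-at-random check and is not built from past values. The Background gives a general association; it does not show that bed days or contacts predict cannabis days in a sample where every patient has a cannabis diagnosis. Consultant contacts exist in one arm only.

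Finally, the 37% is one-year dropout in another trial's control arm, whereas assessments here are at 6 and 10 months. It is a planning figure, not a forecast. These objections limit the point. They do not touch the Discussion's claim for intention-to-treat or the labelling of a carried-forward value as multiple imputation.

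**Conclusion.** The point holds in a limited form. Intention-to-treat does not guard against bias from outcomes that were never observed. At the planned loss, the result for about 22 to 26 patients per arm depends on an assumption that the Discussion does not mention. One of the two stated checks on it is a single imputation under the wrong name.

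The only size that follows from the plan's own figure is 0.37 days of bias per day of between-arm difference in departure from the model's prediction. This assumes 37% loss in both arms. The bias is about zero if the mechanism is the same in both. The 0.5 to 0.8 days in the illustrations rest on assumed correlations and loss rates, and are not estimates for this trial. The documents do not establish that the primary analysis is biased or that the register data would correct it. Auxiliary variables may reduce bias; they cannot guarantee its removal.

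This is a cheap improvement to the sensitivity analyses and a correction of wording. It is not a fault in the primary model or the sample size.

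**What to change.** In the Statistics section:

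- Replace the carried-forward analysis with proper multiple imputation of the 30-day cannabis count, done separately by arm under missing at random. Use baseline TLFB and a short pre-specified set of post-randomisation variables available in both arms: register bed days, register outpatient treatments and usual-care contacts.
- Keep the assumed-increase scenario as the missing-not-at-random check, and let the assumed increase differ by arm.
- Report both as sensitivity analyses beside the mixed model.

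In the Discussion, say that intense follow-up reduces loss, that intention-to-treat keeps every randomised patient in the assigned arm, and that protection against the remaining loss depends on the missing-data assumptions. State that loss will be shown by arm.

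The cost is wording and some modelling on data already planned for collection. The register extract must be ready before the results are final, and some precision is lost if the auxiliary variables prove uninformative, which is why the list should stay short.
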